### OBJECTIVES:

The primary objective is to assess the safety, tolerability and efficacy of an trivalent seasonal influenza vaccine formulated with Advax™ adjuvant by comparison to the trivalent seasonal influenza vaccine alone. A secondary objective is to assess the utility and patient acceptability of a needleless vaccine injector (Pharmajet) by comparison to a standard intramuscular injection with syringe and needle.

#### Primary Endpoints:

- **Efficacy:** Seroconversion and seroprotection rates for each included serotype
- **Safety:** Adverse events and vaccine tolerability

#### Secondary Endpoints:

- Kinetics and persistence of seroconversion, seroprotection and B- and T-cell immunity for adjuvanted versus unadjuvanted influenza vaccine relative to adjuvant dose.
- Degree of cross-protection against drifted influenza strains for adjuvanted versus unadjuvanted influenza vaccine relative to adjuvant dose.
- Subject feedback and perceptions on needleless injector device

### STUDY POPULATION:

Male and female subjects aged 18 years and older

## **FULL PROTOCOL**

### **1. INTRODUCTION**

#### **1.1. Background**

Influenza is a highly contagious and potentially deadly disease that can be spread through coughing or sneezing. It is caused by a virus and is not the same as a common cold. It can cause serious and debilitating complications such as pneumonia, especially in the elderly, young children and those with chronic disease.

The current study is designed to establish the safety and efficacy of the standard commercial trivalent inactivated influenza vaccine (TIV) when formulated with a range of adjuvant doses. We have shown in previous studies that addition of Advax™ adjuvant with various seasonal (TIV) or pandemic (H1N1/2009) influenza, or hepatitis B antigens improved the immunogenicity of these vaccines as assessed by higher antibody titres. This is the basis for extending study of Advax™-adjuvanted influenza vaccine to compare adjuvant doses lower to those previously tested and thereby identify the minimum adjuvant dose required for maximal vaccine enhancement.

Seasonal influenza vaccines are currently administered by intramuscular injection using a syringe and needle approach. New technology has made available a needleless injection system that is able to deliver the vaccine utilising a spring powered energy source to create a fine high velocity jet of liquid that directly penetrates through the skin without the use of a needle. The PharmaJet injector which is already approved for human use by the US Food and Drug Administration (FDA) employs a single-use, sterile, auto-disable needle-free cartridge which results in an superior injection experience for children and needle phobic subjects compared to use of needle-bearing syringes. This technology offers major advantages for both administrator and recipient over existing needle injection approaches and hence we plan to randomise trial subjects to receive their vaccine through either the PharmaJet device or needle and syringe, thereby allowing us to assess the influence on patient satisfaction and comfort of receiving their influenza vaccine through a needleless device.

Adjuvants are a critical ingredient for many vaccines and act by boosting the immune response to vaccine antigens (e.g. influenza vaccine antigens). Despite considerable research, aluminium salts (alum) remain the dominant adjuvants used globally in human vaccines and there is a major need for new adjuvants, in particular, for adjuvants capable of boosting cell-mediated immunity (this is a particular type of immune response where T cells are activated that are then able to attack and destroy the infection). Alum, although good at stimulating antibodies, is poor at stimulating cell-mediated immunity. The majority of current commercial subunit flu vaccines, including those marketed in Australia do not contain an adjuvant.

FLUAD is a subunit influenza vaccine marketed by Novartis in Europe which contains a squalene oil adjuvant known as MF59. MF59 has been shown in clinical trials to induce higher influenza antibody titres when combined with seasonal or pandemic vaccines, albeit at the cost of higher local and systemic reactogenicity as reflected in

increased injection site pain, headaches and fever. Clinical data accrued to date suggests that Advax™ adjuvant may deliver similar benefits to MF59 adjuvant but without the propensity of MF59 to cause adverse reactions.

Advax™ adjuvant is manufactured under GMP from inulin, a natural storage polysaccharide of plants such as chicory and dahlias. Inulin in its soluble form is already approved in many countries for human intravenous use for renal function testing and is known to be an extremely safe and nontoxic compound. When crystallised, inulin develops properties including an ability to enhance the immunogenicity of co-administered vaccine antigens, which forms the basis for its use as a vaccine adjuvant. Previous clinical studies performed at FMC have confirmed the effectiveness and safety of Advax™ adjuvant when formulated with hepatitis B surface antigen, seasonal or pandemic influenza antigens or bee venom antigen. These studies all support the safety, tolerability and efficacy of Advax™ adjuvant in humans.

The 2012 seasonal influenza vaccine that will form the basis of this study is approved by the TGA. In this study, Advax™ adjuvant at either 5mg or 10mg will be formulated with the 2012 seasonal influenza vaccine, to allow us to confirm whether the reduced adjuvant dose delivers an equivalent anti-influenza antibody response. The rationale for testing a lower adjuvant dose is supported by data from a previous trial of a hepatitis B vaccine where Advax™ adjuvant at 5mg and 10mg doses was shown to be effective. If successful, this study would allow us to minimise the adjuvant dose and thereby maximise adjuvant availability, which could otherwise be a limiting factor, for example in an influenza pandemic where speed of production is critical.

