### **1.2.3 Rationale for selection of doses**

Currently available commercial seasonal influenza vaccines contain 15 micrograms of influenza haemagglutinin (HA) from the three influenza virus serotypes (two A serotypes and one B serotype) approved by TGA for that particular year's vaccine. This equates to a total of 45 micrograms of HA per vaccine in 0.5mls volume. As the needleless injector has a capacity of 0.5mls this means that it can inject the full dose of influenza HA. When formulated with Advax for use in the needleless injector, this will reduce the dose of influenza HA by approximately 20% in order to keep the volume to 0.5mls. However, we have previously shown that much greater HA dose reductions (3-10 fold) had little impact on the immunogenicity of influenza vaccine when combined with Advax™ adjuvant.

We have previously demonstrated in other clinical studies that Advax™ adjuvant is safe and effective in the dose range of 5 to 20mg although only the 20mg dose has been tested with influenza vaccines. In this study, we wish to test whether the same benefits can be achieved from a lower 5mg or 10mg dose of Advax™. This would reduce the dose of adjuvant required for each vaccine and thereby provide benefits in terms of reducing the cost of each vaccine and increasing adjuvant availability, for example in a pandemic, where a large number of vaccine doses might be required in a short space of time

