**9.4 Efficacy analysis**

All continuous data will be described by means of summary statistics: N, mean, standard deviation, minimum, median and maximum and 95% confidence intervals. Categorical variables will be presented using the number of observations (N), frequencies (%) and missing data.

The efficacy variables will be described by adequate methods in tables by visit and treatment group. The change from baseline to endpoint (if necessary defined as the last

value carried forward) will also be described by summary statistics. Influenza-specific antibody titres (IgM, IgG, IgG1-4, haemagglutinin inhibition (HI) titre) will be analysed by calculating changes from the background pre-immune serum readings.

All individuals with at least one post-baseline measurement for efficacy will be included in the efficacy population. The analysis will include listings of objective response according to currently pertaining TGA influenza vaccine criteria, (e.g. seroconversion = four fold increase in HI over baseline, seroprotection = post-immunisation HI of 1:40 or greater; potency = fold increase in HI geometric mean titres (GMT). GMT and 95% confidence intervals will be estimated pre- and post-immunisation and compared across groups by ANOVA. The proportion of each vaccine group achieving seroconversion or seroprotection will be compared by Fisher's exact test.

An efficacy analysis to identify differences in treatment response between unadjuvanted and adjuvanted TIV groups and between needle and needless injector groups will be performed on the complete PPP irrespective of age. Additional subgroup efficacy analyses to identify significant differences in treatment response between unadjuvanted and adjuvanted TIV groups and between needle and needless injector groups will be performed stratifying subjects by age.

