All enrolled individuals who received at least one dose of treatment will be included in the safety population. The analysis will include listings and frequency tables of adverse events and laboratory values graded according to the FDA/CBER vaccine toxicity grading scale. Adverse events will be tabulated by time (day) and by severity (mild, moderate and severe). Clinically significant reactions will be defined as measured local reactions >10mm, fever >38°C and severity  $\geq$  moderate for other symptoms. Severe reactions are defined as measured local reactions >50mm, fever >39°C and severity  $\geq$  severe for all other symptoms. Injection site reactions will be combined to give an “any local” reaction category and all other symptoms combined to give an “any general” reaction. The proportion of subjects having an adverse reaction will be estimated by vaccine group, observation period and severity. Subjects will be asked to score injection site pain at the time of injection, and 30 minutes post immunization using a visual analogue scale. Binomial distribution point estimates and 95% confidence intervals will be used to estimate each rate. Percentages will be compared by Fishers exact test.  $P < 0.05$  will be considered statistically significant. No adjustments will be made for multiple comparisons.

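### The rationale asks whether a reduced adjuvant dose gives an equivalent response, but the only between-group comparisons fixed are tests of difference, with no margin or interval rule

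*Protocol*

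**What the plan says.** **The dose aim.** Protocol section 1.1 gives the reason for testing two adjuvant doses: "to allow us to confirm whether the reduced adjuvant dose delivers an equivalent anti-influenza antibody response". The same section wants to "identify the minimum adjuvant dose required for maximal vaccine enhancement". Section 1.2.3 adds: "we wish to test whether the same benefits can be achieved from a lower 5mg or 10mg dose of Advax™".

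**The formal objective.** The synopsis objective compares adjuvanted vaccine "by comparison to the trivalent seasonal influenza vaccine alone". It sets no objective of comparing one dose with the other.

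**The analysis.** Section 9.4 compares GMT across groups by ANOVA. For rates: "The proportion of each vaccine group achieving seroconversion or seroprotection will be compared by Fisher's exact test". The efficacy analysis is described as one "to identify differences in treatment response between unadjuvanted and adjuvanted TIV groups" and between the two injection methods. Section 9.8 repeats ANOVA and Fisher for the age subgroups. Section 9.4 also plans 95% CIs for the GMTs and response listings against TGA criteria.

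**The sample size.** Section 9.7 has six groups of 65, based on a TGA minimum of 50 per group and 20% drop-out. It expressly declines a power calculation.

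**The doses.** Sections 1.1, 1.2.3 and 5.2 give 5 mg and 10 mg. Section 7.2, and the example in section 9.10, give 10 mg and 20 mg. Section 1.2.3 names 20 mg as the only dose tested before with influenza vaccine.

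**The concern.** A test of difference starts from no difference and asks whether the data contradict it. Failing to contradict it shows equivalence only if the trial could hardly have missed a difference that matters. Equivalence or non-inferiority needs a stated largest acceptable loss and a rule that the confidence interval must exclude it. The protocol has neither, and no power basis from which one could be inferred.

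The reader of the final report will want to know whether the adjuvant dose can be reduced, because section 1.1 says success would allow that. With the tools now fixed, the report will have P values from tests of difference and a GMT interval for each group. If the dose groups do not differ significantly, nothing in the protocol separates a real match from a trial too small to see the gap.

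**Working it through.** **Step 1. The plan's own size.** 50/(1 - 0.20) = 62.5, so 63 per group; the stated 65 is close and sufficient. Evaluable per group: 65 x 0.8 = 52. Each formulation has two device groups, so 2 x 52 = 104 evaluable per formulation. Total: 6 x 65 = 390, within the limit of 400. The figure reproduces, but it carries no information on what dose difference the trial could detect.

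**Step 2. Assumptions.** The protocol gives no expected rates, SD or margin, so those below are assumed and shown as ranges. Tests are two-sided at 0.05. The ANOVA is approximated by a two-group comparison of the doses.

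**Step 3. Missing a real loss in response rate.** Exact power of Fisher's test with 104 per arm:

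| Higher dose | Lower dose | Power | Missed |
|---|---|---|---|
| 70% | 60% | 0.278 | 72% |
| 70% | 58% | 0.387 | 61% |
| 90% | 80% | 0.451 | 55% |
| 80% | 70% | 0.329 | 67% |
| 60% | 50% | 0.252 | 75% |
| 70% | 55% | 0.563 | 44% |

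Within a single device (52 per group), a true 10-point loss is missed in 79-86% of trials across the same base rates.

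**Step 4. Width of the interval.** At 70% in both arms the 95% half-width is 1.96 x sqrt(2 x 0.7 x 0.3/104) = 0.125. Two dose groups with identical observed rates would still be compatible with a loss of about 12.5 points.

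**Step 5. Missing a real loss in GMT.** SE of the difference in mean log10 titre = SD x sqrt(2/104). A 1.5-fold loss is log10(1.5) = 0.176.
- SD 0.5: SE = 0.0693; 0.176/0.0693 = 2.54; power = Phi(2.54 - 1.96) = 0.72; missed 28%.
- SD 0.6: SE = 0.0832; 0.176/0.0832 = 2.12; power = Phi(2.12 - 1.96) = 0.56; missed 44%.

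**Step 6. What a proper rule could deliver at this size.** Take non-inferiority on the GMT ratio, with an assumed 1.5-fold margin, a 95% CI and no true difference between doses. The arithmetic is that of step 5, so power for one strain is 56-72%. If all three strains must pass, power is the trivariate normal probability that each standardised estimate clears its limit. With between-strain correlation 0.2-0.8 this is 23-41% at SD 0.6 and 42-58% at SD 0.5, so about 23-58% overall. Adjusting for baseline titre could raise these figures.

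A 10-point non-inferiority margin on a rate is further out of reach: at 70% in both arms, 80% power would need 330 evaluable per dose arm, against 104.

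**The case against.** **The equivalence wording is background, not an objective.** This stands. Section 1.1 asks whether the response is equivalent and does not undertake to show that it is. The formal objective is comparison with unadjuvanted vaccine. In the synopsis, dose enters only through secondary endpoints, and section 9.3 calls the analysis descriptive. A reader might infer that dose equivalence is the trial's primary hypothesis; the documents do not support that. The rationale still offers a conclusion that the analysis cannot deliver.

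**The protocol does not rest on P values alone.** This is also true: GMT confidence intervals, fold rises and TGA criteria are planned. However, the TGA criteria judge each group on its own, and separate GMT intervals are not an interval for the ratio between doses. None is tied to an equivalence decision.

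**A dose comparison may already be covered.** Comparing GMT across groups and the rates of each vaccine group can include the two dose groups. The gap is therefore not that such a test is excluded. The paragraph stating the purpose of the efficacy analysis names other contrasts, and whatever dose test is run is one of difference.

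**The SAP may settle it.** A SAP could order contrasts and add intervals. But the tests are fixed in the protocol, and so is the equivalence wording; that mismatch is visible without the SAP.

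**Two stronger readings go too far.** A reader might infer that the sponsor intends to treat P>0.05 as equivalence. No passage says so; the point is only that no other rule is given. A reader might also take "No adjustments will be made for multiple comparisons" as part of this fault. That sentence stands in section 9.6, on safety, and lack of adjustment makes a finding of no difference harder to reach, not easier. It is no part of this point.

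**Conclusion.** The point holds in a limited form: the rationale raises an equivalence question, and the fixed between-group comparisons are tests of difference with no margin or interval rule. At the planned size a non-significant dose comparison would be weak evidence. A fall from 70% to 58-60% would be missed in 61-72% of trials, and a 1.5-fold lower GMT in 28-44%. These figures rest on 104 evaluable per formulation, which follows from section 9.7, and on assumed rates and SDs, which the protocol does not give. Other base rates move the miss rate for a 10-point loss between 55% and 75% without changing the conclusion.

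The comparison with unadjuvanted vaccine is not affected. The reference for the reduced dose is also unsettled, because the dose statements conflict. If the arms are those in section 5.2, the 20 mg dose tested earlier has no concurrent arm, and a lower against higher comparison would not answer the question in section 1.2.3 as worded.

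**What to change.** 1. Reconcile the adjuvant doses in sections 1.1, 1.2.3 and 5.2 with those in 7.2 and 9.10, and state which dose the reduced dose is compared with. No margin can be set before this is done.
2. Add to section 9.4 a lower against higher adjuvant dose comparison for each strain, reported as the Day 28 GMT ratio and the difference in seroconversion, each with a 95% CI.
3. State that P>0.05 in this comparison is not evidence of equivalence.
4. Choose one of two routes. Either fix in advance a non-inferiority margin, justified on clinical grounds, with a rule for combining the three strains; or replace the equivalence wording in section 1.1 with an aim to estimate the difference between doses.

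**Cost.** Items 2 and 3, and the estimation route, need only text and a few extra table rows, with no more subjects or samples. The stated primary endpoints, including seroprotection, stay as they are. The margin route costs more: a margin must be defended, and the result may well be inconclusive. At an assumed 1.5-fold margin, power is 56-72% for one strain and about 23-58% if all three must pass. If that is too low, the estimation aim is the more honest choice at this sample size.

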## **1.2. Study Rationale**

### **1.2.1 Overall study rationale**

Extensive animal and human data suggests that addition of Advax™ adjuvant to standard influenza vaccines will enhance influenza immunity. This would be of particular benefit to those populations at high risk for influenza morbidity or mortality by providing them with higher levels of protection. Neutralising influenza antibody levels are accepted by the TGA as indicative of the level of vaccine protection.

### **1.2.2 Rationale for schedule and route of administration**

The goal for influenza vaccination is to achieve a protective immune response in a minimum time frame and with the simplest dosing schedule. Animal data using several different models show that there is an increase in both the magnitude of the antibody response as the dose of antigen and adjuvant is increased to a critical levels but beyond this level the antibody response plateaus whilst the risk of adverse reactions continues to rise in a dose dependent manner. Hence it is critical to perform dose ranging studies to identify this “sweet spot” in the antigen and adjuvant dose response. Whilst previous clinical studies have compared different antigen doses, a fixed 20mg dose of Advax™ adjuvant was used. Hence there remains a need to be addressed in this study to now test different doses of adjuvant while keeping the dose of antigen fixed.

New technology has made available a needleless injection that delivers the vaccine through an intramuscular route without the use of a needle, instead utilising a spring powered energy source to inject liquid directly through the skin. The PharmaJet injector

employs a single-use, sterile, auto-disable needle-free syringe that results in an arguably superior injection experience and sensation compared to needle-bearing syringes. This device is FDA approved. Based on the above, we will trial a one dose regime of seasonal influenza vaccine delivered using standard needle and syringe or the PharmaJet needleless injector in a 1:1 ratio for all groups. This will enable us to assess patient satisfaction when using a needleless injector compared to needle-bearing vaccination administration.

### **1.2.3 Rationale for selection of doses**

Currently available commercial seasonal influenza vaccines contain 15 micrograms of influenza haemagglutinin (HA) from the three influenza virus serotypes (two A serotypes and one B serotype) approved by TGA for that particular year's vaccine. This equates to a total of 45 micrograms of HA per vaccine in 0.5mls volume. As the needleless injector has a capacity of 0.5mls this means that it can inject the full dose of influenza HA. When formulated with Advax for use in the needleless injector, this will reduce the dose of influenza HA by approximately 20% in order to keep the volume to 0.5mls. However, we have previously shown that much greater HA dose reductions (3-10 fold) had little impact on the immunogenicity of influenza vaccine when combined with Advax™ adjuvant.

We have previously demonstrated in other clinical studies that Advax™ adjuvant is safe and effective in the dose range of 5 to 20mg although only the 20mg dose has been tested with influenza vaccines. In this study, we wish to test whether the same benefits can be achieved from a lower 5mg or 10mg dose of Advax™. This would reduce the dose of adjuvant required for each vaccine and thereby provide benefits in terms of reducing the cost of each vaccine and increasing adjuvant availability, for example in a pandemic, where a large number of vaccine doses might be required in a short space of time

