### **7.4 Preparation**

A minimum of 30 minutes before administration the vaccine will be transferred from 4°C storage to room temperature for temperature equilibration. Standard TIV will be supplied in a pre-packaged syringe with needle as supplied by the manufacturer. For subjects receiving the adjuvanted vaccine, the adjuvant will be supplied and mixed with vaccine as per the vaccine administration SOP. The vaccine is mixed by repeated inversion before the complete contents of the vial are aspirated into either a new 1ml syringe or the needleless injector device disposable cartridge. The formulated vaccine can be kept at room temperature for 8 hours. Before administration, the adjuvanted vaccine syringe/cartridge should be inverted a number of times to ensure even mixing of

the adjuvant. Standard influenza vaccine is a clear solution whereas the vaccine containing adjuvant is a cloudy white colour.

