### **7.5 Administration of injection**

The total dose will be given as a single injection into or over the deltoid muscle using a suitable disposable sterile syringe mounted with a 25-27G needle if in the standard syringe adjuvanted TIV groups, pre-packaged syringe and fixed needle if in the standard syringe TIV alone group, or the needleless applicator if in needleless injector groups.

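### HA content is about 20% lower in the adjuvanted injector arms and unstated in the adjuvanted needle arms, so the pooled adjuvant and device contrasts do not isolate the randomised factors

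*Protocol*

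**What the plan says.** **Antigen dose.** Protocol 1.2.2 gives the aim as to "test different doses of adjuvant while keeping the dose of antigen fixed". Section 1.2.3 describes the commercial vaccine as 15 micrograms of HA for each of three strains: "This equates to a total of 45 micrograms of HA per vaccine in 0.5mls volume". For TIV alone through the injector it says: "As the needleless injector has a capacity of 0.5mls this means that it can inject the full dose of influenza HA". It makes an exception for adjuvanted vaccine given by that device: "this will reduce the dose of influenza HA by approximately 20% in order to keep the volume to 0.5mls". No section gives the HA content of the two adjuvanted needle arms. Section 7.4 says that for adjuvanted vaccine "the complete contents of the vial are aspirated into either a new 1ml syringe or the needleless injector device disposable cartridge", and leaves the mixing to an administration SOP.

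**Reassurance offered.** Section 1.2.3 says that 3 to 10 fold HA reductions made little difference in the presence of Advax. Sections 1.2.2 and 1.2.3 say that the earlier influenza work used 20 mg Advax only. Section 5.2 randomises to TIV, TIV + 5 mg or TIV + 10 mg.

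**Analysis.** Section 9.4 plans comparisons of unadjuvanted with adjuvanted TIV and "between needle and needless injector groups will be performed on the complete PPP irrespective of age". Section 9.8 repeats a pooled analysis of the total efficacy population. The only stratification named in either section is by age.

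**Hardware.** Under 7.5 the adjuvanted needle arms use a disposable syringe with a 25-27G needle, while the unadjuvanted needle arm uses a "pre-packaged syringe and fixed needle if in the standard syringe TIV alone group". Section 9.5 compares pain scores across groups by ANOVA.

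**The concern.** The design crosses three formulations with two devices. A pooled contrast on one factor is clean only if nothing else changes with it. By the Protocol's own account HA content also changes, in at least two of the six arms, which contradicts the fixed-antigen statement in 1.2.2.

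Adjuvanted against unadjuvanted TIV is the primary objective, and HI response is its efficacy endpoint. If the adjuvanted arms carry less antigen on average, a missing benefit could mean that the adjuvant does little, or that it made up for less HA. If only the injector arms are reduced, a weaker antibody response by injector could likewise come from HA rather than from the device.

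Separately, formulation and syringe type change together within the needle arms, which bears on pain and local reactions by formulation.

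**Working it through.** **Inputs.** 45 micrograms of HA in total, 15 per strain (1.2.3). Reduction of about 20% (1.2.3). Allocation 1:1:1 by formulation and 1:1 by device, six cells (5.2). 65 subjects per cell, from a minimum of 50 and 20% dropout (9.7).

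**The plan's own group size.** 50 / (1 - 0.20) = 62.5, so 63; the plan uses 65. 65 x 0.80 = 52 evaluable, above 50. 6 x 65 = 390, within 400. The figure is reproduced.

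**Reduced dose.** 45 x 0.80 = 36 micrograms; per strain 15 x 0.80 = 12.

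**Mean HA per contrast, equal cells (micrograms).**

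| | Only adjuvanted injector arms reduced | All adjuvanted arms reduced |
|---|---|---|
| Adjuvanted | (45 + 36)/2 = 40.5 | 36 |
| Unadjuvanted | 45 | 45 |
| Difference | -10% | -20% |
| Injector | (45 + 36 + 36)/3 = 39 | (45 + 36 + 36)/3 = 39 |
| Needle | 45 | 39 |
| Difference | -13% | 0% |

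The adjuvant contrast is unequal on both readings. The device contrast is unequal only on the first.

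**Which contrasts keep HA equal.** Device within TIV alone is matched on either reading. Adjuvant within the needle arms is matched only if those arms carry full HA. Comparing 5 mg with 10 mg is matched within a device only if both have the same dilution, which is not stated.

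**Possible effect on titres (assumption).** The Protocol gives no relation between HA and titre. Assume log titre rises with log HA at slope b. The affected cells are then multiplied by 0.8^b. On the first reading, the pooled adjuvant GMT ratio is multiplied by 0.8^(b/2) and the pooled injector/needle ratio by 0.8^(2b/3).

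| b | Adjuvant | Device |
|---|---|---|
| 0 | 1.00 | 1.00 |
| 0.25 | 0.97 | 0.96 |
| 0.5 | 0.95 | 0.93 |
| 1.0 | 0.89 | 0.86 |

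**Precision of within-stratum contrasts.**
- Adjuvant, 65 v 130 instead of 130 v 260: sqrt[(1/65 + 1/130)/(1/130 + 1/260)] = sqrt(2) = 1.41.
- Device in TIV alone, 65 v 65 instead of 195 v 195: sqrt(195/65) = 1.73.

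**Power illustration (assumption).** With 52 evaluable per cell, two-sided 0.05 and seroconversion of 50% v 65%, power for adjuvant is 72% pooled (104 v 208) and 44% in one device (52 v 104). For device it is 77% pooled (156 v 156) and 34% in TIV alone (52 v 52).

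**The case against.** The Protocol discloses the reduction, explains it by the injector's 0.5 ml capacity, and argues that it matters little. Less antigen should work against the adjuvant, so a positive finding would be conservative. The device objective is mainly utility and acceptability, and nothing suggests that HA content alters those. Section 9.4 also plans tables by treatment group, section 9.6 reports adverse events by formulation and route, and stratified models may be in an SAP that is not shown.

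Much of this stands: the direction is as stated, the size is probably modest, and the device effect on antibody is not the main device question. Two things remain. The HA content of a randomised arm is not an SAP detail, and 1.2.2 and 1.2.3 conflict on it. The reassurance also rests on 20 mg Advax, and whether lower doses do as well is this trial's own question; it makes a small effect of a 20% change plausible but does not establish it.

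Stronger readings are not supported:
- **The effects can never be separated.** Six cells are randomised, and on the natural reading HA-matched contrasts exist for both factors. Only if every adjuvanted arm is reduced is adjuvant fully tied to HA.
- **All 260 adjuvanted subjects receive less HA.** This is a possibility left open by silence. Section 1.2.3 mentions the reduction only for the injector.
- **The needle difference causes a pain difference or breaks blinding.** The gauge of the fixed needle is not given and could lie within 25-27G. Section 7.4 already notes that the adjuvanted vaccine is cloudy, so matching hardware alone would not mask it.

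**Conclusion.** The point holds. Sections 1.2.2 and 1.2.3 contradict each other on antigen dose, and the pooled contrasts in 9.4 and 9.8 mix HA content with the randomised factors. The adjuvant contrast is off by 10% or 20% in mean HA, depending on the reading; the device contrast is off by 13% or not at all.

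Assuming that more HA does not lower the response, the bias runs against the adjuvant and a demonstrated benefit stands. What cannot be read cleanly from the pooled analysis is a null adjuvant result or, on the natural reading, a weaker antibody response by injector. The effect on titres is unknown; under assumed slopes of 0 to 0.5 it is 0 to 5% of the adjuvant GMT ratio and 0 to 7% of the device ratio.

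A reader might infer that the pooled contrasts should be dropped. The documents do not support that: the likely bias is modest and the loss of precision substantial. The syringe and needle difference is a secondary matter of interpretation.

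**What to change.** 1. Reconcile 1.2.2, 1.2.3 and 7.4, and state the HA content and volume of each of the six arms. Sections 7.2 and 9.10 give Advax doses that differ from 1.1, 1.2.3 and 5.2; that separate conflict must be settled before the dilution per arm can be stated. No dose or volume is proposed here.
2. In 9.4, beside the pooled contrasts, report adjuvant against none within each device and needle against injector within each formulation, with a formulation-by-device interaction. If only the adjuvanted injector arms are reduced, the HA deficit coincides with that interaction, so the interaction cannot tell an HA effect from a true device-by-adjuvant effect.
3. Identify the contrasts with equal HA: TIV alone for device, and the needle arms for adjuvant if they carry full HA. Describe results from unequal arms as the effect of adjuvant with reduced HA.
4. Interpret pain and local reactions by formulation within the needle arms in light of the different syringes, and compare them also within the injector arms. No hardware change is asked for.

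**Cost.** Text and analysis wording only. Within-stratum intervals are about 1.4 times wider for adjuvant and 1.7 times for device. The interaction is weaker still: its standard error is sqrt[2(1/65 + 1/130)/(1/130 + 1/260)] = 2 times that of the pooled adjuvant contrast, so a non-significant interaction would not show that HA is unimportant.
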